### Data monitoring

A central project data manager is responsible for conducting quality control on all collected data. Both an interim report and a final report are submitted to the Italian Ministry of Health, which funded the project (PNRR-POC-2023-12378461).

Monitoring activities are carried out by personnel from the Scientific Directorate and Surgical Science Technology structure of IRCCS Istituto Ortopedico Rizzoli. These units operate independently from the clinical team responsible for conducting the study procedures.

Additional project auditing is performed by the Clinical Trial Centre, an autonomous body within the Institute. The final study report is also submitted to the Ethics Committee for review.

## Ethics and dissemination

### Research ethics approval and consent

Ethical approval was obtained on June 20, 2024, from the Emilia Romagna Ethics Committee (CE-AVEC), Bologna, Italy (protocol number: 342/2024/Sper/IOR). All participants will give informed written consent prior to enrolment. Participants may withdraw from the trial at any time.

### Protocol amendments

Minor amendments to the protocol will be thoroughly documented. Major amendments—such as revisions to the patient information sheet or consent form, changes in the local project leadership, or the addition of a new study site—will be submitted to the Ethics Committee for formal approval.

### Confidentiality and access to data

Data are recorded using CRFs and processed centrally at the IRCCS Istituto Ortopedico Rizzoli, Bologna, Italy. Participants are not identified by name or any other personal data in any study reports, documentation, or files. Instead, each subject is assigned a unique identification code used throughout the study. A static file securely links each code to the corresponding personal information (e.g., name, clinical chart number, telephone number, address). This file, along with all static and dynamic data related to the multicenter, cross-sectional clinical trial—including derived *in vitro* and laboratory data, records, and images—is stored in a password-protected archive created using 7-Zip software.

The encrypted archive is uploaded to a secure cloud server with user access regulated by role-based permissions and protected through single-step login and password authentication. Only the principal investigator and designated key collaborators directly involved in the study are authorized to access individual-level data. Additionally, the Data Protection Officer of IRCCS Istituto Ortopedico Rizzoli creates and stores a backup copy of the archive on a weekly basis. In cases where data exists only in paper format or other non-electronic media, they are scanned, converted into static PDF files, and archived using the same secure procedures applied to electronic data.

### Dissemination policy

This trial protocol has been developed in accordance with the SPIRIT international guidelines. Study results will be disseminated through peer-reviewed publications and submitted for presentation at national and international scientific conferences. To protect patient privacy, raw data will not be publicly shared; access will be restricted to authorized personnel for internal monitoring and data auditing purposes, as well as to the Ethics Committee. Authorship will follow the criteria outlined in the 2018 Recommendations of the International Committee of Medical Journal Editors (ICMJE).

### Scientific relevance and broader impact

OP continues to represent a significant public health issue, primarily due to its strong association with age-related fractures and the substantial socio-economic burden it imposes (16). Conventional diagnostic approaches—such as BMD measurement via DXA and fracture risk assessment tools like FRAX—exhibit notable limitations (17). BMD alone does not adequately reflect the complex and multifactorial nature of fracture risk, while tools like FRAX fail to capture dynamic variables such as rapid bone loss or sex-specific differences in bone architecture (18). Furthermore, existing OP definitions, particularly those relying on T-scores, were originally developed for Caucasian women, and do not account for critical anatomical and metabolic differences between sexes—potentially compromising diagnostic accuracy across diverse populations. This trial addresses these gaps by proposing an innovative, low-cost, and portable diagnostic approach based on the *in vitro* analysis of PBMCs viability from a minimal peripheral blood sample. Although the current research protocol involves extended laboratory steps, the final goal is the development of a simplified diagnostic kit based on automated PBMC viability assays. This will reduce turnaround times compared to those comparable with routine blood tests. The method, developed and patented by IRCCS Istituto Ortopedico Rizzoli, holds the potential to support early diagnosis, disease staging, and risk stratification of osteopenia and OP in a gender-specific and personalized manner. Its ease of use and minimal infrastructure requirements make it particularly suitable for low-resource settings and remote populations, helping to extend screening and monitoring capabilities where they are most needed.

The implementation of this approach through this trial may significantly enhance public health outcomes by enabling earlier intervention, reducing fragility fractures, and improving patients’ quality of life while lowering healthcare costs. Additionally, it paves the way for a robust pipeline of applications—from population-based screening programs to clinical trial stratification and development of research kits—fostering knowledge transfer and collaboration between public and private sectors.

## Strengths and limitations of this study

*-Innovative Diagnostic Approach*.

This study investigates a novel, patented PBMC-based method for OP screening and stratification. By relying on simple blood collection and *in vitro* PBMC behavior, this approach offers a potentially accessible, low-cost, and portable alternative to current diagnostic tools such as DXA and FRAX, which show important limitations.

*-Gender-Specific and Multi-Parameter Evaluation*.

A key strength is the integration of gender-specific analysis and the correlation of PBMC behavior with platelet indices, lymphocyte subpopulations, inflammatory cytokines, and bone turnover markers. This comprehensive profiling may lead to a more precise understanding of OP pathophysiology and risk across different patient subgroups.

*-Double-Blind Design and Multicenter Validation*.

The study design includes a partial double-blind approach to reduce laboratory and interpretation bias, and involves two geographically distinct centers in Italy, strengthening the reproducibility and generalizability of results across different populations.

*-Non-Randomized Design*.

A limitation is the non-randomized nature of the study, which does not allow for assessment of causality or longitudinal changes. While stratification is rigorous, observational bias cannot be entirely ruled out.

*-Restricted Population and Potential Confounders*.

Although several confounding factors (e.g., BMI, comorbidities, substance use) are excluded by design, the inclusion of only patients with recent DXA and a limited age range (>40 years) may reduce generalizability to younger populations or those without DXA access.

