## Introduction

Osteoporosis (OP) is a major public health problem, and globally every 30 min one person suffers from an OP fracture, determining direct healthcare costs in Europe of about 37.5 billion (1). Although the World Health Organization (WHO) settles the OP diagnosis by Dual-energy X-ray Absorptiometry (DXA) T-score Bone Mineral Density (BMD) assessment, BMD alone has not enough sensitivity/specificity (2); many OP fractures occur with BMD values above OP diagnostic threshold, and test intervals, accuracy and targeted population are still debated (3). Additionally, Fracture Risk Assessment Tool FRAX, often associated with DXA and interesting for its modest cost, does not reach statistical strength needed to screen and identify OP fractures and stages. In addition to the above-mentioned limits linked to OP definition by DXA T-score, other restrictions exist. OP definition by DXA was developed for Caucasian women, although it has been used for other female populations and for men (4, 5). In addition to the well-known role of estrogen in women, which accelerates bone loss (5), men and women also display structural differences in bone growth, catabolism and size. The larger bone structure of men makes BMD results appear better than what they are (8). Likewise, aging men have more periosteal apposition, less cortical porosity and endocortical resorption than aging women (6). Thus, the same T-scores may mean different fracture risks in men and women of the same age. Additionally, T-scores results, both in men and in women, can be differently affected by the presence of co-morbidities (obesity, osteomalacia, etc). Therefore, BMD alone and/or associated with FRAX cannot represent an accurate predictor of OP and related fracture risk.

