#### Inclusion criteria

Ø Healthy, osteopenic and OP (fractured and unfractured) patients;Ø Available DXA (hip and/or lumbar spine) BMD T-score;Ø Men or women > 40 years from two different Italian areas (Bologna, Catania);Ø Body Mass Index (BMI) between 18.5-29.9 Kg/m^2^;Ø Informed consent signed.

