### Statistical methods

Statistical analyses are performed using R software (12) and relevant packages, such as ggplot2 (13), for graphical data visualization. A p-value < 0.05 is considered statistically significant.

A total sample size of 120 patients (n = 30 per group) was calculated using G*Power software (power = 0.80, alpha error probability = 0.05). The estimation was based on a Chi-square test (contingency table) with a medium effect size (w = 0.33), derived from the hypothesized difference in PBMC viability (yes/no) between healthy, osteopenic, and osteoporotic patients (fractured and non-fractured). A 20% potential drop-out rate was also considered in the calculation. This sample size ensures adequate statistical power for the primary outcome while maintaining feasibility across the two recruiting centers.

All data are recorded in an electronic dataset comprising continuous variables (e.g., age, PBMC viability, cell count and size, T lymphocyte subpopulation percentages, expression of pro- and anti-inflammatory cytokines, platelet-related parameters, and bone turnover markers, including BMD T-score), nominal categorical variables (e.g., gender, diagnosis), and ordinal categorical variables (e.g., patient stratification). Univariate analyses are conducted to assess the distribution, central tendency (e.g., mean, median), and dispersion (e.g., standard deviation, variance, interquartile range) of quantitative variables, and the frequency distribution of qualitative variables. Continuous variables showing skewed distributions are transformed to approximate normality.

After assessing normality and homogeneity of variances, appropriate statistical tests are applied. For normally distributed data with equal variances, parametric tests such as ANOVA, General Linear Models (GLM), and Student’s t-test are used. In cases of non-normality or heteroscedasticity, equivalent non-parametric tests (e.g., Kruskal–Wallis and Mann–Whitney U tests) are employed.

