Patients are stratified by BMD T-score and gender. Correlation, regression, and accuracy analyses are performed accordingly. Specifically, the relationship between BMD and PBMCs viability, count, size, differentiation, T lymphocyte subpopulations, inflammatory cytokines, platelet-related parameters, and serum biochemical markers of bone turnover is investigated. Pearson’s correlation coefficient is used for normally distributed data, and Spearman’s rank correlation is applied for non-parametric data. Receiver Operating Characteristic (ROC) curve analysis is conducted to assess the discriminative power of individual variables.

To avoid information loss and potential selection bias, missing values are imputed. When missingness is minimal, single imputation is used; otherwise, multiple imputations are performed, assuming data are missing at random (MAR) (14). Multiple imputation is conducted using the Multivariate Imputation by Chained Equations (MICE) package in R (15).

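### The article says BMI confounding is excluded by design, but eligibility only narrows BMI to 18.5–29.9 kg/m² and the stated correlations and group comparisons name no BMI term

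*Protocol article*

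**What the plan says.** All places are in the protocol article.

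- *Strengths and limitations of this study*, bullet on the restricted population and potential confounders: "Although several confounding factors (e.g., BMI, comorbidities, substance use) are excluded by design". BMI is the first factor named.
- *Inclusion criteria*: "Body Mass Index (BMI) between 18.5-29.9 Kg/m^2". No other design step concerns BMI.
- *Allocation*: four groups of 30 are formed from DXA T-score and fracture status, without randomization. No matching or balancing on BMI is stated.
- *Statistical methods*: "Patients are stratified by BMD T-score and gender. Correlation, regression, and accuracy analyses are performed accordingly". Group comparisons use "parametric tests such as ANOVA, General Linear Models (GLM") and t-tests, or rank tests in their place. Relationships with BMD use Pearson or Spearman coefficients. For accuracy, "Receiver Operating Characteristic (ROC) curve analysis is conducted to assess the discriminative power of individual variables". None of these is described with BMI as a covariate.
- *Introduction*: "T-scores results, both in men and in women, can be differently affected by the presence of co-morbidities (obesity, osteomalacia, etc".

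**The concern.** The article names BMI as a confounder and then says that the design has removed it. A reader who accepts this has no reason to tabulate BMI by group or to adjust for it. The eligibility range removes the underweight and obese tails and keeps the whole normal and overweight span.

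What is at stake is how marker results are read. The secondary objectives relate BMD to PBMC properties, lymphocyte subsets, cytokines and bone turnover markers, and *Statistical methods* adds the platelet parameters. *Exclusion criteria* explains the smoking and diabetes exclusions by the wish to keep confounders out of the interpretation of PBMC behavior. If BMI is associated with T-score within the admitted range, and a marker tracks BMI, that marker will correlate with T-score and differ between groups with no link to bone. The bias can also run the other way and mask a real association.

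**Working it through.** The plan gives no figure for BMI confounding, so there is none to reproduce. The sample size of 120 does not involve BMI.

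**Step 1. What the range keeps.** From *Inclusion criteria*: 29.9 − 18.5 = 11.4 kg/m². At an illustrative height of 1.65 m (1.65² = 2.7225), this is 18.5 × 2.7225 ≈ 50 kg to 29.9 × 2.7225 ≈ 81 kg.

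Assume that BMI before restriction is normal with mean 25.5 to 27 and SD 4 to 5 (not in the documents). Truncating N(26.5, 4.5) to 18.5–29.9 gives SD 2.87. The share of variance left is 2.87² / 4.5² = 8.24 / 20.25 ≈ 41%. Over the whole assumed range it is 34% to 50%.

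**Step 2. Effect on the stated tests.** Simulation assumptions, none of them in the documents:

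- BMI N(26.5, 4.5), cut to 18.5–29.9.
- T-score mean −1.3 to −1.5, SD 1.2.
- 30 healthy, 30 osteopenic and 60 osteoporotic patients sampled on T-score.
- Marker related to BMI only, with no true marker–bone link.
- Correlations as they stand before restriction.

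The ranges show the spread over repeated runs. With 1,000 to 3,000 runs, the Monte Carlo standard error at a rate of 21% is √(0.21 × 0.79 / n), about 0.7 to 1.3 percentage points.

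| BMI–T-score r | BMI–marker r | T-score/marker correlation test, unadjusted | Four-group ANOVA, unadjusted |
|---|---|---|---|
| 0.2 | 0.2 | 5–6% | about 5% |
| 0.3 | 0.3 | 7–8% | 6–7% |
| 0.4 | 0.4 | 13–14% | about 9% |
| 0.4 | 0.5 | about 21% | about 12% |

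With BMI in the model, both tests return to about 5% in every row. The implied healthy-minus-osteoporotic gap in mean BMI is about 0.9 to 2.0 kg/m² for BMI–T-score correlations of 0.2 to 0.4.

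**Step 3. Closed-form cross-check.** Assume a within-group BMI SD of 3.0, a BMI gap D between two groups of 30, and a within-group BMI–marker correlation r. The spurious standardized difference is d = r × D / SD. With r = 0.3 and D = 2: d = 0.3 × 2 / 3.0 = 0.20.

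- Two-group t-test: noncentrality 0.20 × √(30/2) = 0.77, so it rejects in 11.9% of trials instead of 5%.
- Four-group ANOVA with a linear BMI trend: noncentrality 30 × 0.0222 = 0.67, so it rejects in 9.1%.
- AUC: Φ(0.20/√2) = 0.56 instead of 0.50.

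At the weak end (r = 0.1, D = 1), d = 0.03 and the t-test rejects in 5.2%, practically nominal. At the strong end (r = 0.4, D = 3), d = 0.40 and it rejects in 33.2%. These correlations are within-group, so the figures are not directly comparable with the table.

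**The case against.** **The article is condensed, and covariates usually sit in the full protocol or SAP.** This stands. GLM and regression can both carry BMI, and nothing says that BMI will be ignored. The point therefore rests on the sentence that the article does print. A covariate list elsewhere would supply the adjustment but would not make that sentence true.

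**BMI may well be in the dataset.** This also stands. A reader might infer from the variable list in *Statistical methods* that BMI is not recorded, but the list is illustrative, and BMI has to be known to check eligibility.

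**The Introduction does not contradict the design.** This stands. A reader might take its remark on obesity as the article's own proof of residual confounding. The BMI cap removes obesity, however, and the remark does not say that BMI matters within the normal and overweight range. That link is an assumption here.

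**The sentence is shorthand in a bullet about generalizability.** This stands in part. Substance use is likewise only cut at thresholds, and the preceding bullet concedes that some observational bias may remain. But that concession is made about the lack of randomization, and the next bullet lists BMI among the factors removed.

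**The diagnostic aim is untouched.** Largely true. Sensitivity and specificity against DXA-defined groups describe how the test performs, whatever drives it, and need no BMI adjustment. A reader might infer that the primary accuracy estimates are biased; the documents do not support that.

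**The size is assumed.** This stands. At correlations of 0.2 the effect is close to nil, and 21% needs 0.4 and 0.5 together. The simulation also samples all osteoporotic patients on T-score, although *Primary objective* classes fractured patients as osteoporotic whatever their T-score. Drawing the 30 fractured patients regardless of T-score shrinks the BMI gap by about 27–32% (for example from 1.4 to 1.0 kg/m²), with little change in rejection rates.

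**Conclusion.** The concern holds in a limited form. The article claims a property that its design lacks: BMI is restricted, not excluded, and the stated correlations and group comparisons contain no BMI term that would make up the difference. Any residual BMI difference between T-score groups can appear as, or hide, a marker–bone association in those analyses. Whether mean BMI will in fact differ is not known from the documents.

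The consequence is modest and depends on assumptions. It is negligible for markers weakly related to BMI and material only where both correlations reach about 0.4. It bears on the correlation analyses and on reading group differences as bone-specific, not on accuracy against DXA. It is worth correcting because the article itself names BMI as a confounder and the remedy costs almost nothing.

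**What to change.** 1. In *Strengths and limitations of this study*, say that BMI is restricted to 18.5–29.9 kg/m², and take it out of the factors described as excluded.
2. Report BMI by group (mean, SD and range), using the value already measured for eligibility.
3. Show BMI-adjusted results beside the unadjusted ones: partial correlation or regression for the T-score relationships, and a GLM with BMI as a continuous covariate for the group comparisons. Leave the sensitivity and specificity estimates against DXA unadjusted.

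Cost: one model term and one degree of freedom (with 120 participants, 118 to 117 for a correlation and 116 to 115 for the four-group comparison). No new measurement or patient procedure is needed.

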## Patient and public involvement

Patients and/or the public were not involved in the design, conduct, reporting or dissemination plans of this research.
